### Secondary Outcomes Analysis

As one of the aims of the study is to estimate the effect size, the 95% CI (2-sided) of the PDI-G percent change from baseline to T1 (T0-T1), which is planned to be the primary outcome in a subsequent cluster randomized trial and therefore of major interest in this pilot study, will be given. Only questionnaires with at least 6 out of 7 answered items will be considered. Missing items will not be imputed. Questionnaires with less than 6 answered items will not be considered.

As a sensitivity analysis, missing values of the PDI-G will be replaced on item level using multiple imputation based on predictive mean matching using the variables age, sex, center, and pain intensity at baseline as potential predictors. Missing scores and differences can then be calculated using the imputed items. Furthermore, a best- and worst-case scenario will be looked at, where missing values will be imputed by the highest and lowest observed value for T0 and T1 in the best case scenario and vice versa in the worst case scenario (lowest and highest observed value for T0 and T1, respectively). As another sensitivity analysis, a mixed linear regression model for the dependent variable PDI-G score at T1 will be performed including age, sex, and PDI-G at T0 as fixed effects and center as random effect. Descriptive analysis at item level and for the total number of pain-related patients at T0 and T1 will be done. Descriptive analysis of the item and score level will be done for all remaining secondary outcomes. For differences in scores between baseline and follow-up, 95% CIs will be reported. Missing values for secondary outcomes will not be imputed.

No sample size calculation was performed, as the main purpose of the pilot study is to investigate feasibility of the applied interventions and study procedures. Considering the exploratory nature of the pilot study, and based on experiences from previously conducted research, a total of 50 patients is considered sufficient to provide an initial estimate of the potential effect of the intervention measured by the PDI-G percent change from baseline to T1 (T0-T1), which is the key secondary endpoint. Assuming a SD of 13.7 and 15.4 score points [34] corresponding to a SD of 19.6% and 22% score points respectively, a sample size of 50 patients and a 2-sided 95% CI would yield the following: assumed SD 19.6: [x-5.6, x+5.6]; assumed SD 22: [x-6.3, x+6.3], where x is the point estimate of the PDI-G percent change from baseline to T1 (T0-T1).

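### The predictor list for the multiple imputation of PDI-G items does not name the PDI-G itself; followed as written, it weakens this sensitivity analysis of the T0-T1 change

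*Protocol article*

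**What the plan says.** The main PDI-G analysis uses available questionnaires without imputation: "Only questionnaires with at least 6 out of 7 answered items will be considered. Missing items will not be imputed".

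The imputation is a secondary check: "As a sensitivity analysis, missing values of the PDI-G will be replaced on item level". Its method and predictors are given as "multiple imputation based on predictive mean matching using the variables age, sex, center, and pain intensity at baseline as potential predictors". The result feeds the change score: "Missing scores and differences can then be calculated using the imputed items".

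The same section adds a best- and worst-case imputation and a mixed model for PDI-G at T1, "including age, sex, and PDI-G at T0 as fixed effects and center as random effect". So T0 is used as a predictor of T1 in the mixed model but is not named in the imputation model.

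**The concern.** The quantity of interest is a within-patient difference. A missing PDI-G item is best predicted by the other answered items on the same sheet and by the PDI-G at the other visit, and neither is listed. An imputation model that leaves out T0 draws a T1 value that hardly depends on where the patient started, and that value is then subtracted from the patient's real T0.

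Two consequences follow. The T0-T1 correlation among imputed patients shrinks towards zero, which inflates the SD of change. If loss to T1 is related to baseline disability, the mean change shifts as well. At stake is whether a gap between the main result and this check can be read as sensitivity to missing data, or is partly produced by the imputation model.

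**Working it through.** **1. The plan's own precision figure.** Inputs from the paragraph on sample size: n = 50, "Assuming a SD of 13.7 and 15.4 score points [34] corresponding to a SD of 19.6% and 22% score points respectively". The percentages imply a 70-point scale (15.4/70 = 22.0%; 13.7/70 = 19.6%). Half-width = t(0.975; 49) × SD/√50:
- 2.0096 × 19.6/7.071 = 5.57, stated as 5.6
- 2.0096 × 22/7.071 = 6.25, stated as 6.3

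Both reproduce. They concern the change at n = 50 and do not involve the imputation. On the 70-point scale they are about 3.9 and 4.4 points.

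**2. SD of change under completely random loss, closed form.** Assumptions not in the document: score SD 13.7 at both visits; T0-T1 correlation ρ = 0.5 or 0.7; baseline pain intensity correlated 0.4 with T0 and 0.3 with T1; fraction m = 0.2 or 0.3 of T1 missing; age, sex and center uninformative. A T1 value imputed from pain intensity then correlates 0.4 × 0.3 = 0.12 with own T0. With r = (1 − m)ρ + 0.12m, the SD of change is 13.7 × √(2(1 − r)).

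| ρ | m | r | SD, listed predictors | True SD | Inflation |
|---|---|---|---|---|---|
| 0.5 | 0.2 | 0.424 | 14.7 | 13.7 | 7% |
| 0.5 | 0.3 | 0.386 | 15.2 | 13.7 | 11% |
| 0.7 | 0.2 | 0.584 | 12.5 | 10.6 | 18% |
| 0.7 | 0.3 | 0.526 | 13.3 | 10.6 | 26% |

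**3. Simulation closer to the plan.** n = 50, 6 centers, about 20% of T1 missing, predictive mean matching with 5 donors, 10 imputations, 250 runs per scenario, at score level for wholly missing T1. Assumed: score SD 15.4, true improvement 6 points, ρ = 0.5 or 0.7, correlation of pain intensity with T0 of 0.3, 0.5 or 0.7. Loss is either completely random or rises with T0 (log-odds 1.0 per SD). Improvement is expressed as T0-T1. Ranges run over the assumed correlations.

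| | Listed predictors | With PDI-G T0 added |
|---|---|---|
| Random loss: correlation of imputed T1 with own T0 | 0.02-0.25 | 0.36-0.56 |
| Random loss: SD inflation against full data | 7-20% | 2-4% |
| Random loss: mean improvement (full data 5.9-6.1) | 5.8-6.2 | 5.8-6.2 |
| T0-dependent loss: correlation of imputed T1 with own T0 | 0.02-0.21 | 0.28-0.49 |
| T0-dependent loss: SD inflation | 9-24% | 4-6% |
| T0-dependent loss: mean improvement (full data 5.9-6.0) | 6.9-7.65 | 6.3-6.5 |
| T0-dependent loss: bias of the mean | 0.9-1.7 points | 0.35-0.5 points |

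Example (ρ = 0.7, pain correlation 0.3, T0-dependent loss): 7.65 − 5.91 = 1.74 points with the listed predictors and 6.37 − 5.91 = 0.46 with T0 added. Across scenarios the 95% CI half-width with the listed predictors is 5-18% larger than with T0 added (for example 4.97 against 4.75 and 4.58 against 3.87 points).

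**4. Direction.** Under the same T0-dependent loss the complete-case improvement is 4.6-5.2, below the full-data value, and the imputation with the listed predictors overshoots to 6.9-7.65. If patients with low T0 were lost instead, the signs would reverse, because the model is symmetric.

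**5. Not simulated.** Single missing items on a returned sheet. There the list passes over up to six answered items of the same questionnaire.

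**The case against.** The strongest objection is textual. The article speaks of potential predictors and never says that only these four are used. In an item-level multivariable imputation the incomplete items often predict one another by default, and then the PDI-G is already in the model. A reader might infer that the PDI-G is deliberately excluded; the text does not establish that. What stands is that an analyst who follows the printed list would leave it out, and that two analysts could obtain different results from the same sentence.

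A reader might also infer that the plan will overstate the program's effect. The documents do not support this. Under random loss the mean is essentially unbiased; under T0-dependent loss the direction follows an assumed drop-out pattern, for which the article gives no figure. The simulated bias of 0.9-1.7 points also lies well inside the planned half-width of about 3.9-4.4 points.

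A third inference would be that the inflated SD goes into the planning of the cluster trial. Nothing in the article says that the SD from the imputed analysis will be used there. The effect estimate is tied to the non-imputed main analysis.

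The imputation is also not the only robustness check: the mixed model conditions on T0, and a best- and worst-case analysis is planned. This limits the damage, although the mixed model as described targets the T1 score and does not itself give a mean change. Finally, 30% missing goes beyond the article's own drop-out limit of below 20% (Table 3); at 20% the closed-form inflation is 7-18%.

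That a condensed article leaves details to an analysis plan is fair in general. Here, however, it does state a predictor list, and the point concerns that list.

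**Conclusion.** The point holds in limited form. The stated list omits the PDI-G, although the mixed model in the same section uses PDI-G at T0. Followed as written, the imputed T1 values are only weakly tied to the patient's own T0, the SD of change in this sensitivity analysis is inflated by about 7-26% (20-30% of T1 missing), and its CI widens. The mean is biased only if loss depends on baseline PDI-G, by about 0.9-1.7 points in the n = 50 simulation, upward or downward according to who is lost. All sizes rest on assumed correlations, an assumed drop-out pattern and score-level imputation of a wholly missing T1. The main analysis and the 5.6/6.3 precision are not touched by this. It is a worthwhile correction to a secondary check, not a threat to the pilot's conclusions.

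**What to change.** State in the analysis plan that the imputation model also includes (a) the PDI-G total score at the other visit and (b) the mean of the other answered PDI-G items at the same visit, and keep age, sex, center and baseline pain intensity. A total and a mean are preferable to all items at both visits, given about 50 patients. Pain intensity at T1 is optional: it comes from the same T1 questionnaire, so it helps only when that sheet was returned.

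The cost is one sentence and a slightly larger imputation model. The variables are already collected, and the Data Analysis section says that the plan for the primary analysis is still to be finalized before database closure. The change does not remove the problem entirely: in the simulation, which added PDI-G at T0 only, about 2-6% SD inflation and 0.35-0.5 points of bias under T0-dependent loss remained at n = 50.

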### Overall Aim of the Study

The main objective of this pilot study is to test the developed program in a small number of practices with a small number of patients to assess the feasibility of the developed intervention components (eg, assessment and e-learning) and methods used for recruitment (eg, screening process) and data collection. Thus, a control group (no intervention) will not be involved. The evaluation of the program’s potential effectiveness and data generation on the prevalence of the programs’ target group in German general practices are secondary objectives. Based on findings of this study, the program and evaluation concept will be adapted where applicable and applied in a subsequent confirmatory cluster randomized controlled trial (not described in this protocol).

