## Methods

### Study Design

A single-arm, exploratory pilot study with accompanying process evaluation will be conducted to pilot the case management program. Conducting a pilot study provides a good opportunity to assess feasibility of a full-scale study and can be considered an essential prerequisite to enhancing likelihood of success of the main study. Pilot studies should be well designed with clear feasibility objectives, and explicit criteria for determining feasibility [19]. Figure 1 details the design for the RELIEF pilot study.

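### The mixed model planned as a sensitivity analysis of the PDI-G change has no coefficient equal to that change, and the contrast that would give it is not stated

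*Protocol article*

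**What the plan says.** All of this is in the protocol article.

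- **Target.** Secondary Outcomes Analysis opens with "As one of the aims of the study is to estimate the effect size" and names the quantity to be reported as "the 95% CI (2-sided) of the PDI-G percent change from baseline to T1 (T0-T1"). The section adds that this is the intended primary outcome of the later cluster randomized trial.
- **Sensitivity analyses.** The same section lists item-level multiple imputation (with center among the candidate predictors), best-case and worst-case imputation, and then, as a further sensitivity analysis, the model in question: "a mixed linear regression model for the dependent variable PDI-G score at T1 will be performed including age, sex, and PDI-G at T0". The terms are given in full as "including age, sex, and PDI-G at T0 as fixed effects and center as random effect".
- **Design.** Study Design says "A single-arm, exploratory pilot study with accompanying process evaluation will be conducted". Overall Aim of the Study says "Thus, a control group (no intervention) will not be involved".
- **Size.** The recruitment target is 6 practices (Recruitment) and 50 patients (end of Secondary Outcomes Analysis).

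The section mentions no centring, adjusted mean, prediction or contrast for the model. It does not say which output is to be set beside the T0-T1 change.

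**The concern.** A sensitivity analysis should re-estimate the same quantity under different assumptions. Regressing a follow-up score on its baseline is a familiar model when there are two groups, because the group coefficient is then the result. With one arm there is no such coefficient. What remains is an intercept, slopes for age, sex and T0, and two variance components.

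If the model is run and its coefficient table reported as the text stands, the reader gets nothing to compare with the key interval. This matters somewhat more because no other planned outcome model allows for practice. The headline interval would then have no practice-adjusted counterpart, for the outcome on which a cluster trial is to be built.

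**Working it through.** **1. The plan's own figure.** The inputs are n = 50, SDs of 13.7 and 15.4 points, and a two-sided 95% CI (end of Secondary Outcomes Analysis). The stated conversion to 19.6% and 22% implies division by 70: 13.7/70 = 19.6% and 15.4/70 = 22.0%. The half-width is t(0.975, 49) × SD/√50:
- SD 19.6: 5.57, stated as 5.6
- SD 22: 6.25, stated as 6.3

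Both figures reproduce. They come from a simple one-sample interval with no practice term.

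**2. What the planned coefficients mean.** The model is

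T1 = b0 + b1·age + b2·sex + b3·T0 + u(practice) + e.

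Here b0 is the expected T1 at age 0, reference sex and T0 = 0. The terms b1 and b2 are covariate associations, and b3 is the slope of T1 on T0. None is the mean of T0 − T1. If all covariates are centred, the intercept becomes the adjusted mean T1, which is still not the change.

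**3. Illustration** (assumed values: mean T0 35, mean T1 31, slope 0.6; age and sex ignored).
- Intercept: 31 − 0.6 × 35 = 10
- Mean change: 35 − 31 = 4
- Contrast from the same fit: 35 − (10 + 0.6 × 35) = 4

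The coefficient misses the change and the contrast recovers it.

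**4. Simulation of the model as written.** REML was used, with 50 patients, 6 practices and 300 runs per row. Assumptions not taken from the protocol: baseline mean 35, SD 13.7 at both times, ICC 0.05, no age or sex effect. Entries are averages over runs.

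| True change | T0-T1 correlation | Raw mean change | Intercept | T0 slope | Intercept, covariates centred | Mean T0 minus centred intercept |
|---|---|---|---|---|---|---|
| 0 | 0.5 | 0.07 | 16.89 | 0.51 | 34.75 | 0.07 |
| 5 | 0.5 | 5.12 | 11.66 | 0.50 | 29.79 | 5.13 |
| 10 | 0.5 | 10.00 | 7.72 | 0.51 | 24.93 | 9.99 |
| 0 | 0.7 | −0.16 | 11.14 | 0.70 | 35.14 | −0.15 |
| 5 | 0.7 | 5.02 | 5.34 | 0.71 | 30.02 | 5.02 |
| 10 | 0.7 | 9.93 | 0.64 | 0.69 | 24.94 | 9.93 |

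Under these assumptions the intercept is expected to be 35 × (1 − correlation) − change. It therefore mixes the change with the baseline mean and the slope, and it averages 11 to 17 when nothing has changed. The last column tracks the raw change closely in every row.

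**5. The change-score model is the same fit.** Put D = T0 − T1 and centre the covariates. If T1 has centred intercept c0 and T0 slope b3, then D has intercept (mean T0 − c0) and T0 slope (1 − b3). Residual variance, practice variance and the intercept's standard error do not change. In one simulated data set both forms gave a change of 3.850, SE 2.647 and practice variance 31.088.

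**6. A two-time-point model is not automatically equivalent.** With random intercepts for patient and practice only, both cancel when T1 is subtracted from T0, so the time effect carries no practice variation. In the data set of step 5 its SE was 1.672, the same as the plain paired SE and well below 2.647.

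**7. Rough size of the practice effect.** The protocol gives no ICC. With 50/6 = 8.33 patients per practice and an assumed ICC of the change between 0 and 0.05, the variance factor runs from 1 to 1 + 7.33 × 0.05 = 1.37. The half-widths would go from 5.57 to 5.57 × √1.37 = 6.5, and from 6.25 to 6.25 × √1.37 = 7.3. Small-sample degrees of freedom would widen them further; adjustment for T0 may narrow them.

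**The case against.** The strongest reply is that the planned fit already contains the answer. Steps 3 to 5 confirm this: the practice-adjusted change is one linear contrast of the model as specified. A reader might infer that the model yields no estimate of the change, or could neither support nor contradict the key result. The protocol does not support that reading. What is missing is the statement of which quantity to report.

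Four further points on the other side:

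- **The analysis plan may supply the contrast.** It may, and it is not at hand. But the protocol itself fixes the dependent variable, the terms and the role of the model, and as written those three do not fit together.
- **Practice is not ignored elsewhere.** Correct: center is also a candidate predictor in the multiple imputation. It would be wrong to call the mixed model the only analysis that uses practice. It is the only outcome model with a practice effect, and using center to impute items does not adjust the interval for clustering.
- **The model is useful as it stands.** It returns the practice variance of baseline-adjusted T1, which is relevant to planning the cluster trial. This stands.
- **The stakes are low.** Feasibility is the primary objective, no stated decision rule uses this model, and the main PDI-G interval does not depend on it. This stands too, and it limits the weight of the point.

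A reader might also suppose that the model was carried over from a two-arm analysis. The protocol does not say where it came from, and nothing here depends on it.

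**Conclusion.** The point holds as a minor one. None of the coefficients of the stated model is the T0-T1 change, and the protocol does not state the contrast that would produce it. Followed literally, the analysis does not check the key secondary interval, and no practice-adjusted interval for the change is reported.

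The structural finding rests on algebra and the single-arm design, not on assumed values. The sizes in steps 3, 4, 6 and 7 do rest on assumed means, correlations and practice variation, and they only illustrate. The stated half-widths of 5.6 and 6.3 are reproduced and are not in question.

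One qualification concerns scale. The model is on the T1 score, while the key result is called percent change. If percent means points out of 70, as the SD conversion implies, the two differ only by rescaling. If it means percent of each patient's own baseline, the contrast in score points would not match the key result either.

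**What to change.** Restate the sensitivity analysis as follows:

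- **Dependent variable:** T0 minus T1, on the same scale as the key secondary result, with that scale named.
- **Fixed effects:** PDI-G at T0, age and sex, each centred at its sample mean.
- **Random effect:** practice intercept.
- **Report:** the intercept with a small-sample 95% CI (for example Kenward-Roger) as the practice-adjusted mean change, and the practice variance, noting that about 6 practices estimate it imprecisely.

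On the score scale (or points out of 70) this is the planned model reparameterised. Keeping T1 as the dependent variable and stating the contrast, mean T0 minus adjusted mean T1 at the mean covariates, with its CI would serve equally well. A two-time-point mixed model should be used only if it includes a practice-by-time random effect.

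The cost is a rewritten model statement, with the same data and software. The one downside is that the interval may be wider than the simple one.

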**Outcome evaluation**			
	T0 and T1 questionnaires	Percentage of patients who completed T0 and T1 questionnaires	>80%: feasibility given <80%, reasons solvable by modification: feasibility likely 80% and reasons not solvable by modification: feasibility not given
	General practitioner report	Patient drop-out rate	<20%: feasibility given >20%, but reasons solvable by modification: feasibility likely >20% and reasons not solvable by modification: feasibility not given

A range of secondary outcomes will be determined to gather information on potential effects of the program. All secondary outcomes are participant-reported and will be collected before (T0) and after (T1) the intervention by paper-based questionnaires which participants will complete at home and send directly to the study center.

Outcome measures on patient level comprise the German versions of the following validated instruments: Pain Disability Index German version (PDI-G) [24] (key secondary outcome), Patient Activation Measure [25], Short Form 12 Health Survey scale for health related quality of life [26], De-Jong-Gierveld loneliness scale [27], Pain Self-Efficacy Questionnaire German version [28], Avoidance-Endurance Fast Screening instrument [29], Pain-Catastrophising Scale [30], selected items of the European Project on Patient Evaluation of General Practice Care (EUROPEP) questionnaire on evaluation of GP care [31,32], and pain intensity (numeric analogue scale). Further study-specific items will be used to assess the use of self-care such as physical activity (3 items), relaxation techniques (1 item) and use of topical applications (1 item) and patients will be asked to document their pain medication (over-the-counter and prescribed). Secondary outcomes on GP and MA level refer to quality indicators for ambulatory pain management developed in the RELIEF project. Data for the process evaluation will be collected at various points in time as detailed in Figure 1.

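### The stated precision of ±5.6/±6.3 is for PDI-G change in percent of the 70-point scale with 50 analysable pairs, but the endpoint is labelled percent change from baseline

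*Protocol article*

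**What the plan says.** All of this is in the protocol article.

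- **Endpoint.** Secondary Outcomes Analysis says that the pilot will report "the 95% CI (2-sided) of the PDI-G percent change from baseline to T1 (T0-T1"), and that this quantity is planned as the primary outcome of the later cluster randomized trial.
- **Assumed SDs.** The sample size paragraph in the same section reads: "Assuming a SD of 13.7 and 15.4 score points [34] corresponding to a SD of 19.6% and 22% score points respectively".
- **Resulting interval.** For n = 50 and a two-sided 95% level, the paragraph then gives "assumed SD 19.6: [x-5.6, x+5.6]; assumed SD 22: [x-6.3, x+6.3"]. It explains the symbol x in these words: "where x is the point estimate of the PDI-G percent change from baseline to T1 (T0-T1").
- **Analysable questionnaires.** For the main PDI-G analysis, "Only questionnaires with at least 6 out of 7 answered items will be considered", and missing items are not imputed. Multiple imputation and best-case and worst-case imputation are sensitivity analyses.
- **Expected numbers.** Results gives 50 patients as the recruitment target. Table 3 rates drop-out below 20% as feasible and applies a limit of above 80% to this indicator: "Percentage of patients who completed T0 and T1 questionnaires".

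**The concern.** Two different quantities can be called a percentage here. One is the change in points as a share of the whole scale. The other is the change as a share of the patient's own score at T0. The stated SDs belong to the first, while the wording of the endpoint describes the second. The two coincide only when the baseline score equals the scale maximum.

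The stated interval is the quantitative support offered for 50 patients as a basis for an initial effect estimate, and the same quantity is meant to become the primary outcome of the next trial. A reader who takes the label literally will attach an SD of about 20% to a relative change, for which it was not derived. The figure also treats every recruited patient as contributing a usable T0/T1 pair, although the plan has an exclusion rule for the main analysis and a tolerance for drop-out.

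**Working it through.** **Inputs from the article:** SDs of 13.7 and 15.4 points, n = 50, two-sided 95% interval, seven PDI-G items, drop-out limit of 20%. The article does not give the scale range, the expected baseline mean, or whether the SDs describe a change or a score at one time.

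**Step 1: the percentage conversion.** 13.7/0.196 = 69.9 and 15.4/0.22 = 70.0, so the divisor is 70. Conversely, 13.7/70 = 19.57% and 15.4/70 = 22.0%.

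**Step 2: the plan's own interval.** Half-width = t(0.975, n−1) × SD/√n, with t(0.975, 49) = 2.0096.

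- SD 19.6: 2.0096 × 19.6/√50 = 5.57
- SD 22: 2.0096 × 22/√50 = 6.25

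These are the stated 5.6 and 6.3. A normal quantile would give 5.43 and 6.10, which do not match. The arithmetic is correct for percent of scale with 50 pairs.

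**Step 3: if change relative to own baseline is meant.** Approximate the SD of relative change by the SD of change in points divided by the baseline mean. Compared with Step 2, the half-width grows by 70/baseline mean. The baseline means below are assumptions, and 13.7/15.4 are taken as SDs of change.

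| Assumed baseline mean | 70/mean | n = 50 | n = 40 |
|---|---|---|---|
| 28 | 2.5 | ±13.9 / ±15.6 | ±15.6 / ±17.6 |
| 35 | 2.0 | ±11.1 / ±12.5 | ±12.5 / ±14.1 |
| 50 | 1.4 | ±7.8 / ±8.8 | ±8.8 / ±9.9 |
| 70 | 1.0 | ±5.6 / ±6.3 | ±6.3 / ±7.0 |

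Example: 13.7/35 = 39.1%, and 2.0096 × 39.1/√50 = 11.1.

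**Step 4: if the SDs are single-time values at T0 and T1.** SD of change = √(13.7² + 15.4² − 2ρ × 13.7 × 15.4). This is 14.6 points at ρ = 0.5 and 9.3 points at ρ = 0.8. The relative half-widths at n = 50 are then:

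- baseline 35: ±11.9 (ρ = 0.5) to ±7.6 (ρ = 0.8)
- baseline 45: ±9.2 (ρ = 0.5) to ±5.9 (ρ = 0.8)

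At the last of these there is practically no understatement.

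**Step 5: loss of pairs, in percent of scale.** A 20% loss from 50 leaves 40 pairs, with t(0.975, 39) = 2.0227.

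- SD 19.6: 2.0227 × 19.6/√40 = 6.27
- SD 22: 2.0227 × 22/√40 = 7.04

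The interval widens by a factor of 1.13.

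**Step 6: the same precision in points, taking the SDs as SDs of change.**

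- 50 pairs: 2.0096 × 13.7/√50 = 3.9 and 2.0096 × 15.4/√50 = 4.4
- 40 pairs: 2.0227 × 13.7/√40 = 4.4 and 2.0227 × 15.4/√40 = 4.9

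**The case against.** The strongest reply is that the authors meant percent of scale throughout. The SDs are described in percent score points, the endpoint carries the gloss T0-T1, and the Data Analysis section uses that same gloss for a difference. On this reading the interval is right for 50 pairs. This stands as a possible reading, and no sentence in the article states a division by the patient's own T0 score. It does not clear the text, because percent change from baseline is then the wrong name for the endpoint, and both the analysis and the precision statement use it.

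A reader might go further than the article allows in four ways:

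- **That the true interval is about twice as wide.** This needs a baseline mean near 35 and SDs of change. The article gives neither, and Step 4 shows that the gap can nearly vanish.
- **That only complete questionnaires are analysed.** Six of seven items suffice, and imputation is planned as sensitivity analysis. The exclusion is narrower: "Questionnaires with less than 6 answered items will not be considered".
- **That this precision is the only ground for 50 patients.** The paragraph also cites the exploratory purpose and previous research experience, and says that no sample size calculation was made.
- **That the cluster trial will be undersized.** That trial is not described here, and the pilot will report its own observed SDs.

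It is also fair that 20% is a feasibility limit and not a forecast of loss, so 40 pairs is the edge of what the plan accepts.

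**Conclusion.** The point holds as a mismatch between the endpoint label and the stated precision; the calculation itself contains no error. One of the two must change, and the article does not show which.

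- **Relative change meant:** ±5.6/±6.3 does not apply. The half-width at n = 50 is about 1.4 to 2.5 times larger for assumed baseline means of 50 to 28 if the SDs describe change. It is less if they are single-time values with a high T0-T1 correlation.
- **Percent of scale meant:** the figures are right for 50 pairs and the endpoint is misnamed.
- **Either reading:** no loss is allowed for. At the 20% limit the percent-of-scale figures become ±6.3/±7.0, a modest widening.

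The pilot is exploratory and its primary objective is feasibility. No test, power figure or feasibility decision rule depends on this interval. The correction still matters because effect estimation is a stated aim and the endpoint is intended for the next trial.

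**What to change.** 1. Define the key secondary endpoint on one scale wherever it is named. The T0 minus T1 difference in PDI-G points is preferable; a difference stated explicitly in percent of the 0-70 scale would also do. Keep relative percent change as description at most.
2. State whether 13.7 and 15.4 are SDs of change or of scores at a single time.
3. Restate the precision for the expected number of analysable pairs. In points, with the SDs taken as SDs of change, this is ±3.9/±4.4 for 50 pairs and ±4.4/±4.9 for 40.
4. If relative percent change is kept as the endpoint, recompute the interval with an SD for that quantity and give its source.

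The cost is a few sentences in the endpoint definition and the sample size paragraph. No extra patients or data are needed. Where loss is allowed for, the stated precision becomes slightly less favourable.
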